#### Secondary outcomes

Waist circumference will be measured using a 2 m flexible tape measure with buckle, around the midpoint between the iliac crest and inferior margin of the lower rib. Hip circumference will be measured around the widest point of the buttocks. Measurements will be recorded twice in cm to one decimal point (eg, 95.2 cm). A third measure will be taken if the difference is >0.5 cm.

Health-related quality of life will be measured using the EuroQol five-dimensions (EQ-5D) questionnaire and quality-of-life thermometer.^52^ This measure is used frequently in health-related research to explore five dimensions: mobility, self-care, usual activities, pain and anxiety/depression. An additional measure of capability well-being will be measured using the ICEpop CAPability measure for Adults (ICECAP-A)^53^ scale. This is a new scale which, compared with the EQ-5D, explores less clinically related changes in quality of life over four dimensions: feeling settled and secure; being independent; achievement and progress; and enjoyment and pleasure. This might be an appropriate measure in our population due to the potentially large range of participant characteristics. Mental health will be measured using the General Health Questionnaire,^54^ a validated and frequently used 12-item self-report questionnaire.

We will gather data on NHS resource use and participant-borne costs using a specially designed resource questionnaire. These data will help us establish key cost drivers of the intervention.

At 12 months, we will use the Usability, Satisfaction and Ease of Use (USE) questionnaire^55^ to assess feasibility and acceptability of the app and website. We will also use the Heaviness of Smoking Index^56^ and Alcohol Use Disorders Identification Test^57^ questionnaires at 12 months using this opportunity to assess the feasibility of additional questionnaires for data collection. These may be helpful in identifying other potential lifestyle changes made my participants in a future trial related to ‘spillover’ effects of the intervention.

### Process evaluation measures

The process evaluation will explore in detail the way in which the intervention operates to produce outcomes, as well as to assess feasibility and acceptability. The evaluation will be conducted based on MRC guidelines for process evaluations of complex interventions^58^ and will examine the following elements: (i) context; (ii) fidelity of the intervention; (iii) exposure to the intervention; (iv) reach; (v) recruitment and retention; (vi) contamination; (vii) the control arm; and (viii) mechanisms of impact. Table 4 presents the multiple points of data collection for the process data. In brief, some quantitative data will inform the process evaluation (eg, intervention usage statistics). The remaining process data will be gathered via qualitative interviews with participants and helpers, and questionnaires exploring mediators of change (details below).

**Table 4 T4:** Process evaluation measures

Measure	Example questions to be answered	Method
Context	What type of phone/platform did participants use, for example, Android, iOS? How did participants/helpers access the website for example, on phone, on desktop, on tablet? Were there any differences between social networks and what impact did these have on outcomes?	Quantitative analysis Social Network Analysis Qualitative interviews with participants and helpers
Fidelity	Was the intervention delivered as intended? When, if any, were any adaptations needed to the planned intervention?	Descriptive analysis of data usage statistics from software company Qualitative interviews with participants and helpers, and study team
Exposure	How often did participants/helpers use the app and website? How often did participants/helpers access the goal setting/monitoring feature of the app and website? How often did participants/helpers interact with each other via the app and website? What were the patterns and trends of usage over time?	Analysis of data usage statistics from software company
Reach	How well does the study sample represent the population of interest? To what extent did the intervention reach and influence people other than recruited participants, including helpers? What were the particular difficulties/issues that arose during the study in delivering the intervention?	Descriptive statistics Qualitative interviews with participants and helpers
Recruitment and retention	What are the difficulties in recruitment? What is the attrition rate overall and by group? What venues do participants chose to meet for their fieldworker appointments? What are the reasons for withdrawal? What factors were involved in ongoing engagement with the intervention?	Quantitative analysis Qualitative interviews with participants and helpers
Contamination	What are the characteristics of other groups’ people are attending, for example, slimmer’s groups? Have any of the control group seen intervention content from other participants or acted as a nominated helper?	Quantitative analysis Qualitative interviews with participants and helpers
Control arm	What is happening in the control arm?	Qualitative interviews with participants
Mechanisms of impact	What role does social network play in how participants use the intervention? How did participants perceive their social support for healthy eating and physical activity changed throughout the intervention?	Mediators of change questionnaires (see table 3)

#### Qualitative interviews with participants 

At 6 months, we will interview up to 30 participants (depending on data saturation). Participants will be purposively sampled for a range of characteristics (eg, level of app/website use, age, gender). We will also specifically seek to interview those who did not take up the intervention to explore the reasons for this. At 12 months, we will also interview up to 20 participants (10 participants who continued to use the website/app after 6 months, and 10 who ceased to use it). Semistructured interview guides will be used at both time points to explore participant insights related to acceptability of the outcome measures, acceptability and usability of the app and website, patterns of usage, impact of the intervention on behaviour, support received from helpers and barriers to use. Mediators of change will also be explored in the qualitative interviews.

#### Qualitative interviews with helpers 

At 6 months, we will interview up to 20 helpers, purposively sampled for a range of characteristics (eg, level of app/website use, age, gender). A semistructured interview guide will be used to explore helper insights related to acceptability, guidance provided for being a helper, types of support provided to their friend, challenges of supporting their friend and/or using the app and website, and changes in their own health behaviour as a result of being a helper.

Interviews will be completed by trained researchers via the telephone or face to face at a preferred venue (eg, their home or university). Interviews will be audio recorded and transcribed verbatim. A separate informed consent process will take place for the qualitative interviews.

#### Questionnaires exploring mediators of change

Exploratory analysis of mediators is important to identify the processes by which the intervention brings about change. These will help to further refine the logic model for a future full trial. Data on social support, self-efficacy and motivation will be collected at the same time as the main outcome data using the following questionnaires respectively: Exercise & Eating Habits Social Support Scale,^59^ Weight^60^ & Exercise Efficacy Lifestyle Scales^61 62^ and the Treatment Self-Regulation Questionnaire.^63^

#### Social network data

We will explore the characteristics of participants’ social networks at the beginning of the intervention and at the 12-month follow-up using a Social Network Analysis.^64^ Participants will be asked to draw a sociogram of their own ‘ego’ social network, highlighting various elements such as positive and negative influences and network density. Participants will also complete a questionnaire to explore additional characteristics of the individuals they intend to nominate as their helper(s), for example, frequency of contact and type of relationship. All data on participants’ social networks will be gathered anonymously via the use of initials (no names will be collected).

#### Web/app analytics 

We will collect app and website usage data for both helpers and participants using Google Analytics to assess engagement with the intervention. Key usage data includes number of logins to the website and app by helper and participant, duration of login, average sessions per user, pages viewed and how often, whether participants set goals and entered weights, number of helpers nominated, contacts between helpers and participants via the app, number of views of ‘progress charts’ by participant and helper, and patterns of use over time.

### Economic evaluation

The economic analysis aims to identify and measure the key cost drivers of the intervention and control arms as well as identify suitable outcome measures for a future economic evaluation. A costing exercise will be undertaken to provide an indication of the direct costs of the intervention. This will involve monitoring all resources used in delivering the intervention and valuing them in relevant units. In addition to this, an estimation of any intervention effects on NHS and Personal Social Services (PSS) resource use (eg, GP visits) and personal costs (eg, gym membership and food purchases) will be collected via a specially designed resource use questionnaire. Together, these will indicate the relative importance of the economic evaluation in any future trial. A value of information analysis^65^ will further provide information on the likely return on investment in the intervention. The economic analysis will assess the feasibility of using the EuroQol EQ-5D instrument^52^ and the ICECAP-A^53^ instrument as a means of capturing any short-term effects the intervention may have on health-related quality of life and/or capability well-being. The economic evaluation will adhere to guidelines for good economic evaluation practice as outlined by Gold *et al*.^66^ Specific guidance will also be sought from the National Institute for Health and Care Excellence economic evaluation public health reference case^67^ since it is anticipated that this intervention is likely to impact costs and outcomes beyond the NHS and PSS and thus require a broader public sector evaluative perspective.

## Quantitative analysis

A detailed Statistical Analysis Plan has been drafted and will be finalised before the study statisticians are given access to the study group allocations.*Baseline characteristics* will be summarised overall and by randomised group. Participant characteristics will be summarised in relation to socio-demographic, lifestyle, occupational, health status and quality-of-life variables.*Feasibility measures* will be the primary focus of the analysis. Follow-up rates at 12 months will be reported overall and by randomised group, with 95% CIs. The association between baseline factors and follow-up will be assessed using logistic regression, with follow-up (yes/no) as the response variable. A multivariable regression model will be developed to identify independent predictors of follow-up. Use of the intervention will be summarised for the intervention group, overall and in relation to selected baseline characteristics. The availability and utility of data relating to data usage for the app and website will be explored, and a range of summary measures will be presented in the final statistical outputs.*Efficacy outcomes* will be summarised overall and by randomised group, and compared using linear regression models, with randomised group, the baseline measurement of the outcome, age and gender as predictor variables. Regression models will also adjust for the minimisation factors. The residuals from each regression model will be assessed for normality. Where necessary, the outcome measure (at follow-up and at baseline) will be transformed to improve model fit. All analyses will be conducted under intention-to-treat principles and complete case analysis used, unless >20% of cases are lost due to missing data, in which case multiple imputation will be performed. These analyses are exploratory and underpowered, so no formal hypothesis testing will be performed but effect sizes will be reported in line with Consolidated Standards of Reporting Trials guidelines for reporting feasibility and pilot studies (http://www.bmj.com/content/355/bmj.i5239).*Process evaluation measures* will be descriptively analysed to summarise use of the app and website. A per-protocol analysis will also be conducted using simple proxies for adherence (eg, website login/% of webpages accessed) in order to identify the treatment effect associated with adherence.*Potential mediators of change*, such as social support, motivation and self-efficacy, will be used in an exploratory mediation analysis to assess whether they might lie on the causal pathway and to test the logic model.^68^ This will assist in the decision as to whether we need the mediation measures in a future full trial.*Social Network Analysis* will be performed on participant sociograms and egocentric questionnaires. Sociogram data will be captured using pen and paper and later transferred to an ego-network software package such as VennMaker or EgoNet. Data will then be exported for analysis. We will calculate network measures on the alter level (eg, homophily) and the network level (size, density, EI-Index, diversity, components, proportions of ties with specific attributes). Multivariate analyses will then be run on both alter and network level data.*The cost data* will be summarised and described using mean values and variation around these estimates. Key fixed and variable costs of developing the intervention will be described and summarised. EQ-5D and ICECAP-A outcome data will be reported by within-attribute response rates, mean values and associated variance. Within-trial economic analyses will be performed using STATA V.12.0 and reported in line with recent CHEERS guidelines^69^ and the UK public health reference case.^70^ Missing data will be handled using multiple imputation (for both cost and outcome data).^71 72^ Cost–utility estimates will be presented on a cost-effectiveness plane using the UK’s threshold for willingness to pay for an incremental quality-adjusted life-year.

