Promote autonomy	Encourage customisation of goals Ability to add own goals Encouragement and advice via daily app messages/tips Website and app designed in an autonomy supportive way Personalisation of settings	Guidance on website to support participant to set own goals in an autonomy supportive way Encouragement and advice via daily app messages/tips
Provide social support (instrumental and emotional)	Guidance on website Encouragement and advice via daily app messages/tips	Guidance on website Encouragement and advice via daily app messages/tips
Support ongoing goals around physical activity, diet and well-being	Guidance on website Encouragement and advice via daily app messages/tips	Guidance on website Encouragement and advice via daily app messages/tips

Overall, the website will provide evidence-based information for participants and helpers on healthy eating, physical activity and guidance on how to select and/or be a good helper (see below for details). The app will be used to set and monitor weight loss goals, and as a platform to promote interaction with nominated helpers. Example screenshots from the app and website are provided in the online supplementary appendices 3–7.

The HelpMeDoIt! intervention will be delivered via a smartphone app and website. The core aspect of the intervention involves participants nominating one or more ‘helpers’ from among people they know to support them with their weight loss goals. Overall, the intervention will have seven key elements, including: (i) support for goal setting and planning; (ii) ‘track your progress’ for monitoring; (iii) ‘nominate your helper’ to identify social support; (iv) obtain agreement from nominated helper(s) to provide support; (v) helper-specific advice on how to provide effective support; (vi) behaviour-specific information (including ‘tips’ and case stories); and (vii) the goal updates and support element of the intervention.

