### The control group

The control group will receive a leaflet about the health benefits associated with healthy eating and physical activity behaviour change. They will not receive any social support or personalised content. Participants in the control group are not restricted in any way regarding their involvement in other weight loss activities. They can continue to embark on weight loss strategies, for example, join a slimming club. Controls can access the website and app after follow-up is complete at 12 months.

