### Sample size

We intend to recruit 120 participants. Since we are most interested in the intervention, we will recruit using a 2:1 ratio with 80 participants in the intervention group and 40 in the control group. We expect a dropout rate of 30%. This final sample size of 84 for analysis is not powered to detect any differences between groups for the proposed effectiveness outcomes (BMI, physical activity and diet) but will provide enough precision to estimate any feasibility proportion (eg, proportions retained/found the study acceptable/provided outcome data) across the whole sample to within ±11 percentage points using a 95% CI. This would also allow for the estimation of the mean of a continuous outcome (such as BMI) in the intervention arm to within 0.262 of an SD.

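### The per-protocol analysis on usage proxies cannot identify an effect of adherence: in effect it sets self-selected users against an unselected control arm

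*Protocol article*

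**What the plan says.** Under process evaluation measures in the Quantitative analysis section, the protocol article first plans descriptive summaries of app and website use. It then adds: "A per-protocol analysis will also be conducted using simple proxies for adherence (eg, website login/% of webpages accessed"). The stated aim is "in order to identify the treatment effect associated with adherence". The article gives no comparator, cut-off or method for dealing with selection into adherence, and mentions no complier or instrumental-variable analysis.

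The control group section fixes who can have usage data before the outcome is measured: "Controls can access the website and app after follow-up is complete at 12 months".

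On what participants are meant to do, the intervention group section says "The core aspect of the intervention involves participants nominating one or more" helpers. The same section places goal setting, monitoring and helper nomination in the app, and detailed information on the website.

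The Quantitative analysis section also places all analyses under intention-to-treat principles and describes the efficacy comparisons as exploratory and underpowered, without formal testing. The main models adjust for the baseline value of the outcome, age, gender and the minimisation factors.

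**The concern.** Logins and pages viewed are post-randomisation behaviour. They can be used to remove less engaged people from the intervention arm, but no control can be classified or removed on them. The people who remain in the intervention arm are likely to be the more motivated, while the control arm keeps its full mix of motivation. The contrast is then the treatment effect in users plus whatever difference users would have shown without the app. Baseline adjustment removes the part that the covariates explain, but not unmeasured motivation.

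The article fixes both the method and the causal purpose, and the method cannot deliver that purpose. At stake is how the result is read. The section on progression criteria remarks that an app effective for only a minority of users might still be worthwhile. A selection-driven effect in users could be taken as support for that argument.

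**Working it through.** **Inputs from the Sample size section.** The target is 120 people, split 2:1 into 80 and 40, and 30% are expected to drop out. Of the number left, the article says: "This final sample size of 84 for analysis is not powered to detect any differences between groups".

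**The plan's own figures reproduce.**
- Analysed: 120 × 0.70 = 84. With equal dropout by arm (assumed), 80 × 0.70 = 56 and 40 × 0.70 = 28.
- Proportion: 1.96 × √(0.25/84) = 0.107, the stated ±11 points.
- Intervention-arm mean: 1.96/√56 = 0.262 SD, as stated.

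**Assumptions not in the documents.** These are the share classed as adherent (π) and the link between engagement and outcome. The article's usage criterion (more than 50% with two or more app visits, or 25% with three or more) only suggests a range for π. The SD below is the one that remains after baseline adjustment.

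**Selection shift with zero true effect, continuous engagement.** If engagement correlates r with the outcome and the top share π count as adherent, the expected shift of users against all controls is r × φ(z)/π, where z is the normal cut-off for π.
- π = 0.50: φ(z)/π = 0.798. For r = 0.2, 0.3, 0.4 the shift is 0.16, 0.24, 0.32 SD.
- π = 0.30: φ(z)/π ≈ 1.16. The shift is 0.23, 0.35, 0.46 SD.

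**Same point with two groups.** If would-be adherers differ from non-adherers by δ when untreated, the shift is (1 − π) × δ. For δ = 0.3 SD it is 0.225, 0.15 and 0.075 SD at π = 0.25, 0.50 and 0.75. Over δ = 0.2 to 0.5 SD and those values of π it runs from 0.05 to 0.375 SD.

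**Simulation check** (56 v 28, SD 1, π = 0.5, δ = 0.3, 20,000 trials; negative favours the intervention).
- True effect 0: per-protocol mean −0.15, complier estimate 0.00.
- True effect in users −0.30: per-protocol mean −0.45, complier estimate −0.29 (median −0.295).

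**Precision of the complier estimate.** The intention-to-treat standard error is √(1/56 + 1/28) = 0.231 SD, half-width 1.96 × 0.231 = 0.45 SD. The complier estimate is the intention-to-treat effect divided by π, so its half-width is about 0.454/π: 1.81, 0.91 and 0.60 SD at π = 0.25, 0.50 and 0.75. If baseline and 12-month values correlate 0.9 (assumed), these become 0.79, 0.40 and 0.26 of the unadjusted SD.

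**Why the adherence definition matters.** Suppose adherers gain 0.30 SD and people classed as non-adherers still gain 0.15 SD from partial use. At π = 0.5, intention to treat gives 0.5 × 0.30 + 0.5 × 0.15 = 0.225 SD, and 0.225/0.5 = 0.45 SD, overstating the true 0.30. A strict definition, such as a goal set plus a helper registered, invites this error.

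**The case against.** - **The comparator is inferred.** The article does not say that users will be compared with all controls, and the unseen analysis plan may define the set or an adjustment. That stands as a caution. But with no usage data in controls, no between-arm contrast on these proxies can apply the same selection to both arms, and the causal purpose is printed in the article.
- **The website proxies are examples.** A reader might infer that adherence will be judged on web browsing although the core of the intervention runs through the app. The text does not support this: the proxies are introduced as examples, and the Web/app analytics section collects app logins, goals set and helpers nominated.
- **Nothing formal depends on the result.** A reader might infer that a false effect could trigger the full trial. None of the eight criteria in Table 2 uses an effect estimate, and no hypothesis test is planned. The remark about a minority of users explains the debate over the usage criterion and sets no efficacy rule. This objection stands and lowers the severity.
- **The false benefit is conditional.** It needs a positive link between engagement and outcome beyond the adjusted covariates, and the documents give no value. For a strongly tracking outcome the absolute size is also smaller: at a baseline correlation of 0.9 the residual SD is √(1 − 0.81) = 0.44 of the unadjusted SD, so 0.16 to 0.32 becomes about 0.07 to 0.14. This stands. The direction of the tendency does not change.
- **The complier estimate has its own assumptions.** It needs the exclusion restriction and negligible control contamination, which Table 4 treats as an open question. This stands and shapes the fix.

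**Conclusion.** The point holds in a limited form. The planned per-protocol contrast cannot identify the effect that the article assigns to it, because adherence is self-selected and observable in one arm only. If engaged participants would do better anyway, it leans towards the intervention by about 0.16 to 0.32 SD at 50% adherence and 0.23 to 0.46 SD at 30%, on the baseline-adjusted scale with assumed correlations of 0.2 to 0.4. These figures illustrate the size and do not predict it.

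Two stronger readings go too far. The analysis need not show benefit for an inert app: that depends on the assumed selection. A complier analysis does not recover the effect unconditionally either: it does so only under its assumptions, and imprecisely at this sample size. Because the analysis is secondary and exploratory and enters no progression criterion, the severity is minor to moderate.

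**What to change.** 1. Delete the claim that the per-protocol contrast identifies a treatment effect. If the contrast is kept, label it descriptive.
2. Add a complier average causal effect estimate by two-stage least squares, with randomised arm as instrument and the same covariates as the main model. Use the same missing-data handling: the expected 30% dropout exceeds the article's 20% trigger for multiple imputation.
3. Define adherence primarily as any app or website use, so that people classed as non-adherent have had little or no exposure and the exclusion restriction is credible. Keep goal-plus-helper and login or page thresholds as sensitivity definitions only.
4. State the assumptions (exclusion restriction, negligible control contamination) and report the contamination findings from the process evaluation beside the estimate.

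The cost is some wording and a few lines of code. The article says the analysis plan is drafted but not final, and the usage data are already to be collected. The downside is a wide interval (about ±0.9 SD at 50% adherence and ±0.6 SD at 75%, before baseline adjustment, against ±0.45 SD for intention to treat) and an estimate that concerns any use rather than full engagement.

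### The planned per-protocol analysis on usage proxies cannot identify a treatment effect of adherence; its result should be labelled an association with usage, or replaced by a randomisation-based estimate with stated assumptions.

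*Protocol article*

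**What the plan says.** The protocol article, under Quantitative analysis (process evaluation measures), states: "A per-protocol analysis will also be conducted using simple proxies for adherence". Its examples are website login and the percentage of web pages accessed, and its stated purpose is "in order to identify the treatment effect associated with adherence". It gives no comparator, adherence threshold, estimator or adjustment for selection.

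The section The control group says: "Controls can access the website and app after follow-up is complete at 12 months".

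The efficacy models in Quantitative analysis adjust for the baseline value of the outcome, age, gender and the minimisation factors. Table 3 lists motivation and self-efficacy as measured at baseline, but they are not among the stated covariates. The efficacy analyses are described as exploratory, with effect sizes reported and no formal testing.

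**The concern.** A per-protocol set built on usage keeps the engaged part of one randomised arm. The people in the control arm who would have engaged cannot be picked out, because they had nothing to log in to. The contrast then mixes any effect of the intervention with the difference between people who engage and people who do not. Changing the proxy or the threshold does not remove this.

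The design gives a reason to expect such a difference. In The intervention group, points are awarded for entering progress data and for achieving goals, so success can feed back into use. Motivation, an obvious common cause of use and outcome, is not a listed covariate.

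Reporting effect sizes without tests gives no protection, since the bias sits in the point estimate. At stake is how an effect in users would be read. The progression section raises the possibility that the app is worthwhile if it works for the minority who engage, and this analysis would appear to speak to that.

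**Working it through.** **Inputs from the protocol article**
- Allocation (Sample size): "we will recruit using a 2:1 ratio with 80 participants in the intervention group and 40 in the control group".
- Expected dropout (Sample size): 30%.
- Usage levels in progression criterion 6 (Table 2), borrowed here as illustrative adherent shares: more than 50% visiting at least twice, or 25% using the app three or more times.

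**Assumed, because the documents give no figure**
- D: mean outcome of users minus non-users had nobody received the intervention, in SD, net of covariates and signed so that positive is better. Range −0.25 to 0.75.
- Equal dropout in both arms.

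**Step 1. Reproduce the plan's precision.** Analysed: 120 × 0.7 = 84, of whom 80 × 0.7 = 56 intervention and 40 × 0.7 = 28 control. Proportion: 1.96 × √(0.25/84) = 0.107, which agrees with "across the whole sample to within ±11 percentage points using a 95% CI". Mean: 1.96/√56 = 0.262, which agrees with "in the intervention arm to within 0.262 of an SD".

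**Step 2. Bias with no true effect.** Let M_A and M_N be the mean outcomes of users and non-users. The intervention arm mean is pM_A + (1 − p)M_N, and randomisation makes the expected control mean the same. Adherers minus controls is therefore M_A − pM_A − (1 − p)M_N = (1 − p)(M_A − M_N) = (1 − p)D.

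| p | D = −0.25 | D = 0 | D = 0.25 | D = 0.5 | D = 0.75 |
|---|---|---|---|---|---|
| 0.25 | −0.19 | 0 | 0.19 | 0.38 | 0.56 |
| 0.50 | −0.13 | 0 | 0.13 | 0.25 | 0.38 |
| 0.75 | −0.06 | 0 | 0.06 | 0.13 | 0.19 |

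**Step 3. Check with a second model.** Let adherers be the top share p of a normal propensity to use the system, correlated ρ with the residual outcome. The expected spurious difference is ρφ(z₁₋ₚ)/p. At ρ = 0.3 it is 0.38, 0.24 and 0.13 SD for p = 0.25, 0.5 and 0.75. Dividing by (1 − p) gives an implied D of 0.51, 0.48 and 0.51, so ρ = 0.3 corresponds to D of about 0.5 and the two models agree. In 20,000 simulated null trials per setting (56 against 28), the ρ = 0.3 estimate favoured the intervention in 88%, 82% and 70% of trials. At ρ = 0 the mean bias was 0.00 and the figure was about 50%.

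**Step 4. Put the size in context.** At p = 0.5 and D = 0.5 the bias of 0.25 SD is close to the plan's 0.262 SD. That figure is the half-width for one arm's mean, however. For 28 adherers against 28 controls the half-width of the difference is 1.96 × √(1/28 + 1/28) = 0.52 SD, so the bias is about half of it.

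**Step 5. The randomisation-based alternative.** With non-adherence in one arm only, the simplest CACE estimate is the intention-to-treat difference divided by p. Its mean in the null simulations was within 0.03 SD of zero. This is expected, since the numerator averages zero, and it does not test the method's assumptions. The unadjusted intention-to-treat half-width is 1.96 × √(1/56 + 1/28) = 0.454 SD, so the CACE half-width is about 0.454/0.5 = 0.91 SD at p = 0.5 and 0.454/0.25 = 1.81 SD at p = 0.25.

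**The case against.** Several stronger readings are tempting, and the article does not support them.

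- **That the plan compares app users with all controls.** A reader may infer this because controls have no planned access, but the article does not write the comparator and its example proxies concern the website. The SAP, which is not shown, may define both. What stands without the SAP is the article's own claim about what a per-protocol analysis on usage delivers.
- **That the analysis will show a benefit even if the intervention does nothing.** This needs D > 0 after covariate adjustment. The documents give no D; the bias is zero at D = 0 and reverses below it. The gamification rules make a positive D plausible but do not establish it.
- **That a progression decision rests on this figure.** None of the eight criteria in Table 2 uses an effect estimate. The remark about a minority of engaged users is one side of a debate that the article then balances with the other.
- **That non-adherence is strictly one-sided.** Table 4 asks whether any controls saw intervention content or acted as helpers, so some control exposure is treated as possible.

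The case against CACE also has force. It assumes that allocation has no effect in people below the usage threshold. That is doubtful at high thresholds, because helpers may give support by phone, by text or in person. With any use as the definition the assumption is safer, but one-time users count as compliers, and the article cites about 25% of users opening an app only once. If dropout is related to use, a completers-only CACE is exposed to selection too. The interval would be wide. These points mean that CACE should come with stated assumptions; they do not rescue the identification claim.

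**Conclusion.** The concern holds as a point about a stated claim. Usage is self-selected after randomisation and has essentially no counterpart in controls, so a per-protocol contrast on usage proxies does not identify a treatment effect of adherence. It can show a benefit where there is none. With D of 0.5 SD the spurious difference is 0.38, 0.25 and 0.13 SD at adherent shares of 25%, 50% and 75%. These sizes are illustrative: they rest on an assumed D, on adherent shares borrowed from criterion 6, and on the inferred comparator.

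The consequence is limited. This is a secondary analysis in a feasibility trial whose own text says "This final sample size of 84 for analysis is not powered to detect any differences between groups". The wording still deserves correction, because a plausible bias is similar in size to the precision that the plan quotes and correction costs little.

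**What to change.** 1. Delete the statement that the per-protocol analysis identifies a treatment effect. Label any adherers-only result a descriptive association with usage.
2. If an effect of adherence is wanted, specify a CACE in the SAP: two-stage least squares with randomised arm as the instrument and the covariates of the efficacy model.
3. Fix a binary usage definition before allocations are seen, with any use as base case and higher thresholds as sensitivity analyses.
4. State the exclusion restriction and say why it weakens at higher thresholds, given helper support outside the system.
5. Handle missing outcomes as in the main analysis. At the expected 30% dropout, the plan's own rule of imputing when more than 20% of cases are lost would apply.
6. Use the contamination data in Table 4 to check control exposure before treating non-adherence as one-sided.

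Cost: SAP wording and a few lines of code, with no new data, since usage is already collected (Web/app analytics). The price is a wide interval, about ±0.91 SD unadjusted at p = 0.5, which should be reported as it stands.
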